#### Blinding

While the nurse-mentor cannot be blinded to group assignment, ICU staff recording the usual care clinical data in the hospital chart (ICDSC, diagnosis of delirium) will be blinded, as well as the research assistant collecting outcome data. Finally, a numerical code will be assign to each group to allow blinding during data analysis.

### Data collection and analysis

#### Statistical methods

The planned analyses concerning all the primary objectives include descriptive statistics, which, along with 95% CI, will be used to portray the intervention and study design’s acceptability and feasibility criteria. Control and experimental group descriptions will be achieved using descriptive statistics reflected by n, mean, standard deviation, and median, minimum, and maximum for continuous variables and frequencies and percentages for categorical variables; 95% CIs will also be presented when appropriate. Finally, to evaluate the validity of cerebral _r_SO_2_, a Pearson or Spearman correlation will be used (depending on level of measurement) to correlate oximetry scores and scores obtained on the ICDSC, DI, and CAM-ICU at Days 1, 2, and 3 following the onset of delirium.

The planned analyses for the study’s secondary objective of preliminary efficacy will include the statistical methods detailed below. It should first be noted that this is a pilot study assessing the feasibility of a larger study and statistical analyses will be used to examine the preliminary effects of the intervention and determine any trend in the results as this study is not powered for statistical testing. For H1 relative to delirium severity, a repeated measure ANCOVA will be performed using the DI scores taken on Days 1, 2, and 3 following delirium onset. The initial scores on the ICDSC taken at delirium onset will be used as a covariate. Post-hoc tests will be performed if the omnibus test is significant for the group by time interaction. Such an interaction would imply that delirium severity is different between groups over the three days. Mixed models will be used so that a patient with missing data at Days 1, 2, and 3 following the onset of delirium will not be excluded from the analysis. The intent-to-treat principle will be respected; all the patients in the study will be included in the analysis according to their group of randomization. Because the pilot study will not be used to definitely assess the efficacy of the intervention (this would be the objective of the larger study), we plan to conduct a sensitivity analysis using the last observation carried forward.

For hypothesis H2 on adverse clinical complications following onset of delirium, a combined outcome measure will be used (mention in the hospital chart of sternal wound dehiscence, a fall, respiratory tract infection, or accidental removal of urinary catheter, drain, arterial line or endotracheal tube = yes/no) and groups will be compared using a χ^2^ test.

Student’s T-tests for independent groups will be used for hypothesis involving continuous variables H3 on length of ICU and total hospital stay, H4 on psycho-functional recovery 1 month after the onset of delirium, H5 on caregiver’s anxiety level, and H6 relative to caregiver’s sense of self-efficacy. The planned treatment for missing data for hypotheses H3 to H6 is assigning the value corresponding to the group mean.

Assumptions underlying the planned models will be checked and alternative methods may be used if more appropriate. A significance level of 0.05 will be used for all analyses.

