These studies open the door to a novel way of delivering more personalized non-pharmacological delirium management interventions in ICU settings. The involvement of a caregiver who knows about the patients’ personality, life, and family, may offer a reassuring presence, thereby contributing to reality orientation. The present paper describes a study protocol of a delirium management nursing intervention involving caregivers of post-cardiac surgery patients with the hope of diminishing delirium severity and its related clinical complications as well as improving caregiver psychological outcomes. The protocol also tests the validity of regional oximetry (_r_SO_2_) measures obtained with near infrared spectroscopy (NIRS) which may provide an objective indicator for early detection and continuous monitoring of delirium. Finally, several feasibility issues such as delirium detection, risk factors for delirium, and ethics challenges with informed consent are discussed.

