### Sample: eligibility criteria

Patients and family caregivers must be 18 years or older, have the ability to speak and read French, and have the physical and cognitive ability to give informed consent. Additionally, all patients must be scheduled for coronary artery bypass grafting (CABG) or heart valve surgery, must spend their full postoperative stay in the study hospital (i.e., not be transferred to another hospital), and present postoperative delirium defined by a score of 4 or higher on the Intensive Care Delirium Screening Checklist (ICDSC) [19] and confirmed by a medical diagnosis.

Eligible caregivers will be identified as such by the patient, and must be available twice daily for 3 consecutive days after delirium onset to visit the patient and receive pre- and post-bedside visit interventions.

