Evidence suggests that low oximetry levels are linked with a greater risk of delirium, [44] and while this technology could potentially improve delirium detection and monitoring as well as guide decisions about intervention, it must first be piloted before being introduced in a larger scale study. Oximetry values will be obtained for six different sites represented in Figure 1: low right frontal cerebral (1), high right frontal cerebral (2), low left frontal cerebral (3), high left frontal cerebral (4), one arm (5a or 5b), and one leg (6a or 6b). Electrodes will be placed on the higher and lower frontal cerebral areas to cover a larger zone. To obtain the _r_SO_2_ value for each of these six sites, the electrode is left in place for more than 20 seconds for stability of signal, after which the number appearing on the device is recorded. From these six _r_SO_2_ values, two mean scores are calculated: the total cerebral score being the mean score of all four cerebral sites, and the total peripheral score being the mean score of the two peripheral sites. Lower cerebral values and normal peripheral ones are indicative of poorer cerebral oxygenation not due to peripheral hypoperfusion. Given the novelty of cerebral _r_SO_2_ obtained using NIRS, we will describe the validity of this approach by contrasting the scores with three standard tools for the detection and assessment of delirium: the ICDSC, the Delirium Index (DI), and the Confusion Assessment Method (CAM-ICU). These tools will be used at Days 1, 2, and 3 following the onset of delirium.

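### The oximetry validity analysis uses neither the peripheral score jointly nor within-patient change, and the design can support only an association with severity after onset

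*Protocol article*

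**What the plan says.** **Who is measured.** Under the eligibility criteria patients must "present postoperative delirium defined by a score of 4 or higher" on the ICDSC, with a medical diagnosis to confirm it.

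**When.** Table 1 schedules oximetry on Days 1, 2 and 3 only. For the three comparison tools, Methods (Outcomes) states: "These tools will be used at Days 1, 2, and 3 following the onset of delirium".

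**What is recorded.** Six sites are read. The four frontal sites give a cerebral score and the arm and leg give a second one, "the total peripheral score being the mean score of the two peripheral sites". The same paragraph explains the purpose: "Lower cerebral values and normal peripheral ones are indicative of poorer cerebral oxygenation not due to peripheral hypoperfusion".

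**How validity is judged.** Statistical methods names one technique, a Pearson or Spearman coefficient chosen by the type of variable, with this purpose: "to correlate oximetry scores and scores obtained on the ICDSC, DI, and CAM-ICU at Days 1, 2, and 3 following the onset of delirium". Its opening words present this as the evaluation of cerebral oximetry, and the peripheral score is given no role.

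**What is claimed.** Study objectives confines validity to people who have delirium, and Study limits in the Discussion does the same. Other places reach further. The Background says that oximetry "may provide an objective indicator for early detection and continuous monitoring of delirium", the abstract and the end of the Discussion speak in similar terms, and Table 4 lists validity of the measure as a marker of delirium without that restriction.

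**The concern.** Three features of the stated analysis do not match the use described for the measure.

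1. **Specificity.** The protocol's reading of a cerebral signal depends on two scores at once. A two-variable correlation of the cerebral score with a delirium scale cannot apply that. If general low perfusion lowers both scores and worsens delirium, the cerebral score will correlate with severity and look valid.
2. **Monitoring.** Monitoring asks whether a patient's score moves with that patient's delirium. A correlation across patients on one day contains no such contrast.
3. **Detection.** No reading precedes onset and no patient without delirium is enrolled for comparison, so nothing can be learned about how well oximetry signals that delirium is coming or present.

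The protocol says the technology must be piloted before it enters a larger study, so a coefficient reported as evidence of validity would feed that decision.

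**Working it through.** **Inputs from the protocol article:** 30 dyads (Sample size); readings on Days 1 to 3 (Table 1; Outcomes); significance level 0.05 (Statistical methods), taken as two-sided because sidedness is not stated.

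**The plan's own figure.** The only precision stated is for caregiver consent: 1.96 × √(0.75 × 0.25 / 30) = 0.155, which reproduces the ±15.5%. No precision is given for the oximetry correlations.

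**Step 1. What one daily correlation can show with 30 patients.** Fisher interval: tanh(atanh r ± 1.96/√(n − 3)), with 1.96/√27 = 0.377.

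- r = −0.3: tanh(−0.310 ± 0.377) = −0.60 to 0.07.
- r = −0.5: tanh(−0.549 ± 0.377) = −0.73 to −0.17.
- Smallest |r| with p < 0.05: t/√(n − 2 + t²) = 2.048/√(28 + 4.195) = 0.36.

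These widths are ordinary for a pilot and are not the defect. They give the scale for Step 2.

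**Step 2. Can general hypoperfusion pass as validity?** Assume one systemic factor G that drives the cerebral score C, the peripheral score P and severity S (opposite sign), each with loading a and independent noise, and no cerebral-specific effect at all. With unit variances:

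- corr(C, S) = −a²
- partial corr(C, S given P) = −a²(1 − a²)/(1 − a⁴) = −a²/(1 + a²)
- corr(C − P, S) = 0

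| Loading a (assumed) | Cerebral alone | Peripheral as covariate | Cerebral minus peripheral |
|---|---|---|---|
| 0.4 | −0.16 | −0.14 | 0.00 |
| 0.6 | −0.36 | −0.27 (0.36/1.36 = 0.265) | 0.00 |
| 0.8 | −0.64 | −0.39 | 0.00 |

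A simulation of 2 million draws agrees to rounding. At loading 0.6 the expected coefficient equals the 0.36 threshold from Step 1, so a nominally significant result would be about as likely as not with no cerebral signal present.

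The zero in the last column depends on equal loadings. With loadings 0.8 (cerebral), 0.6 (peripheral) and 0.6 (severity), corr(C − P, S) = −(0.8 − 0.6) × 0.6 / √(2 − 2 × 0.8 × 0.6) = −0.12/1.020 = −0.12, against −0.8 × 0.6 = −0.48 for the cerebral score alone. The difference then removes most of the artefact, not all of it.

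**Step 3. Between and within patients.** If both measures have share b of their variance between patients, a single-day correlation is b·ρ_between + (1 − b)·ρ_within. With ρ_within = 0 it still equals b·ρ_between, so a non-zero daily coefficient is compatible with no tracking over time. The same section already uses mixed models for the Delirium Index over the same three days under H1.

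**Step 4. Detection.** Sensitivity, specificity and lead time need readings before onset or in people without delirium. Setting the eligibility criteria beside Table 1 shows that neither is scheduled.

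**The case against.** The strongest reply is that the formal objective is narrow. It concerns validity among people with delirium, and correlations after onset do address that. The early-detection language is prospective and cautious, and no passage promises to estimate detection accuracy. This stands. The mismatch is therefore with Table 4 and the motivating text, not with the objective.

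A second reply is that the phrase about oximetry scores could cover the peripheral score, and that an article may leave such detail to a fuller document. The first half is possible, but separate correlations for each score would still not apply the joint reading in Outcomes. The second half has less force, because the article does state the method, the variables and the days. The clause allowing alternative methods concerns model assumptions, not the quantity being estimated.

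Some stronger readings are tempting but unsupported:

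- **That 30 × 3 = 90 patient-days will be pooled as independent.** The text reads most naturally as one correlation per day, and nothing states pooling.
- **That the coefficients are biased by restricted range.** This would need all surgical patients to be the target, which the objective rules out, and a spread ratio that the documents do not give.
- **That a low cerebral value has no meaning without a normal peripheral one.** Outcomes offers the pattern as a guide to interpretation and does not go that far.
- **That delirium is present at every reading.** It is required at entry, but the intervention section allows for resolution before the sixth encounter. Such readings still follow onset and do not inform early detection.

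**Conclusion.** The point holds in a limited form. The stated analysis can show whether oximetry is associated with delirium scores on each day after onset. It cannot distinguish a cerebral signal from general hypoperfusion, and it cannot show that the measure follows a patient's course. The design cannot examine early detection or the presence of delirium as such.

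The size of the first problem depends on assumed loadings: a spurious correlation of −0.16 to −0.64 over loadings 0.4 to 0.8, with 0.36 enough for nominal significance at 30 patients. The documents give no data on how strongly perfusion drives either score, so this shows what is possible and does not estimate what will happen. The monitoring and detection points rest on the schedule and the stated method alone.

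This is an exploratory part of a pilot, so the consequence is a misread validity result, not a failed trial. It is worth correcting because validity is in the primary objective and the readings needed are already planned.

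**What to change.** 1. Keep the per-day correlations and label them descriptive.
2. Add a repeated-measures analysis of the Delirium Index and the ICDSC over Days 1 to 3: a mixed model with a patient random effect and the oximetry measure split into the patient's mean and the daily deviation, or a repeated-measures correlation.
3. Use the cerebral-minus-peripheral difference as the oximetry measure, and repeat with the cerebral score and the peripheral score as covariate as a sensitivity analysis. State that neither fully removes shared perfusion effects when the scores are noisy or respond unequally to perfusion.
4. Bring Table 4 and the Discussion into line with Study objectives: the conclusion is association with severity and course after onset, and early detection is left to a study with readings before onset or in patients without delirium.

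**Cost.** A little more analysis and some rewording; all six site readings are already collected. Estimates will be imprecise, since 30 patients with three days give at most 30 × (3 − 1) = 60 within-patient contrasts, and the claim becomes narrower.

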### Study objectives and research hypotheses

The primary objective of this pilot study is to examine the acceptability and feasibility of i) the study design; ii) the experimental nursing intervention; and iii) a novel measure, cerebral _r_SO_2_ obtained by NIRS, a non-invasive method to detect cerebral oxygen imbalances among patients with delirium as well as its validity among patients with delirium.

The secondary objective of this pilot study is to examine the preliminary effect of the intervention on patient and caregiver outcomes. The following are the research hypotheses for the study’s secondary objective:

For patient outcomes

Compared with controls, patients in the intervention group will present:

Less severe delirium in the 3 days following onset;Fewer complications (defined as either a sternal wound dehiscence, fall, respiratory tract infection, or accidental removal of urinary catheter, drain, arterial line or endotracheal tube) in the 3 days following onset of delirium;Shorter total length of ICU and total hospital stay;Enhanced psycho-functional recovery one month after the onset of delirium;

For caregiver outcomes

In comparison with controls, caregivers in the intervention group will present:

(H5)A lower anxiety level after the intervention (Day 4 following delirium onset), at Day 15, and at 1 month following delirium onset;(H6)A higher sense of self-efficacy after the intervention (Day 4 following delirium onset), at Day 15, and at 1 month following delirium onset.

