#### Intervention structure

The intervention structure is described in Table 1 and was based on previous studies with caregiver involvement with delirium [18, 20] or dementia [17] and on the level of involvement that was deemed acceptable to family caregivers and acute care patients who are in a precarious state after cardiac surgery. The duration of each encounter was selected to allow time for the caregiver to become comfortable with behaviors within the timeframe allowed for visiting hours and to allow time to reflect on the bedside visits. The intervention consists of a total of seven encounters involving the nurse, caregiver and patient. The first encounter will begin within 24 hours of delirium onset followed by five others at a rate of two encounters a day over the next three consecutive days. A seventh encounter will take place just before hospital discharge. The duration of each of the first six encounters is planned as follows: a pre-bedside mentoring session of 30 minutes; a 15 minute bedside visit with the patient (to abide by the ICU’s visitation hours policies); and a post-bedside session of 15 minutes. The seventh encounter before discharge will last 30 minutes. The nurse-mentor accompanying the caregiver will act as his mentor and is a nursing PhD candidate experienced both with cardiac surgery patients and delirium. In addition, she has received the same 3 hours of training offered by the research hospital to the staff on a regular basis.

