**Table 1 Tab1:** **Schedule of enrolment, interventions and assessments**

Study timepoints	Study period: ***A template is adapted from the SPIRIT guidelines***[21]								
	Enrolment	Allocation		Post-allocation					Close-out
	***-t*** _***1***_	0	***t*** _***1***_	***t*** _***2***_	***t*** _***3***_	***t*** _***4***_	***t*** _***5***_	***t*** _***6***_	***t*** _***7***_
Participant timeline	***Delirium onset***		***Day 1***	***Day 2***	***Day 3***	***Day 4***	***Discharge from hospital***	***Day 15***	***Day 30***
*Enrolment:*									
Eligibility screen/Informed consent:									
Caregivers	√								
Patients							√		
Allocation of participants		√							
*Intervention encounters:*									
Control group									
Intervention group			√	√	√		√		
*Assessments:*									
Baseline using a sociodemographic questionnaire	√								
1. Primary Objectives: Acceptability and feasibility of:									
1.1 –the study design	*	*	*	*	*	*	*	*	*
1.2 –the intervention			*	*	*	*	*		
1.3 –rSO2 using the INVOS 5100 device from Covidien, Mansfield MA USA			√	√	√				
2. Secondary Objectives									
H1- Delirium Severity assessed using the Delirium Index scale [22]			√	√	√				
H2- Complications obtained from a keyword search in the medical chart									√
H3- Length of stay obtained from the medical chart									√
H4- Recovery assessed using the Sickness Impact Profile scale [23, 24]									√
H5- Anxiety assessed with the State Trait Anxiety Inventory State [25]	√					√		√	√
H6- Self-efficacy assessed with a scale adapted from Bandura [26]	√					√		√	√

√: Research activity or questionnaire completed at this timepoint.

*: Assessed with indicators detailed in Table 4.

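### H1 predicts a lower level of delirium severity over Days 1-3, but the only effect the analysis names is the group-by-time interaction, which is zero when the benefit is the same each day

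*Protocol article*

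**What the plan says.** - **Hypothesis.** Study objectives and research hypotheses: compared with controls, intervention patients will show "Less severe delirium in the 3 days following onset".
- **Model.** Statistical methods: "a repeated measure ANCOVA will be performed using the DI scores taken on Days 1, 2, and 3 following delirium onset". Mixed models are to be used so that patients with missing days stay in the analysis.
- **Covariate.** "The initial scores on the ICDSC taken at delirium onset will be used as a covariate".
- **Follow-up rule.** "Post-hoc tests will be performed if the omnibus test is significant for the group by time interaction".
- **Reading of the interaction.** "Such an interaction would imply that delirium severity is different between groups over the three days".
- **Level.** "A significance level of 0.05 will be used for all analyses". The same section says that the study lacks power for testing and that the analyses look for preliminary effects and trends.
- **Timing of the outcome.** In Table 1 the row "H1- Delirium Severity assessed using the Delirium Index scale [22" is marked at Days 1, 2 and 3 only, with nothing at onset.
- **Timing of the intervention.** Intervention structure: "The first encounter will begin within 24 hours of delirium onset". Table 1 marks encounters on Days 1, 2 and 3 and before discharge.

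The text gives the group effect averaged over Days 1-3 no role, and does not say what is concluded about H1 if the interaction is not significant.

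**The concern.** H1 is about level: are intervention patients less delirious over the three days? The interaction is about change: is the group difference on one day unlike that on another? The two coincide only if the series starts with a score taken before any treatment effect. Here no such score is scheduled, and the baseline covariate is on a different scale from the outcome.

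The sentence that interprets the interaction is true as an implication. If the group difference varies across days, it cannot be zero on all of them. It misleads as a criterion because the converse fails: groups can differ on every day with no interaction. An interaction is also silent on direction, since crossing profiles or a pattern favouring control would produce one too.

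At stake is what the pilot passes to the larger trial. If the intervention works from the first encounter and keeps working to the same degree, the stated rule triggers no follow-up comparison.

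**Working it through.** **The plan's own figures.** The article gives no power, effect size, SD or within-patient correlation for H1. Its only sample-size figure, the precision for the caregiver consent proportion, reproduces: 1.96 × √(0.75 × 0.25 / 30) = 0.155, the stated ±15.5%. It has no bearing on H1.

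**What the interaction tests.** Let δ1, δ2, δ3 be the group differences in Delirium Index on Days 1, 2 and 3, and δ̄ their mean. H1 concerns δ̄ (or each δj). The interaction tests δ1 = δ2 = δ3. With n per arm, SD σ and equal within-patient correlation ρ, its non-centrality is

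λ = (n/2) × Σ(δj − δ̄)² / [σ²(1 − ρ)].

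**Equal benefit on all days.** If δj = δ for every day, each term δj − δ̄ is 0, so λ = 0 for any δ, σ, ρ or n. The test then rejects at its significance level, 0.05. This step needs no assumed value.

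**Simulation.** From the article: 30 dyads, three days, level 0.05. Assumed: 15 per arm, SD 1, ρ of 0.4, 0.6 or 0.8, covariate-outcome correlation 0.4, no missing data, no block effect. The interaction F test (2 and 56 df) is set against the group effect from ANCOVA on the three-day mean, with 5,000 runs per setting. Ranges for the group effect run from ρ = 0.8 to ρ = 0.4.

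| Equal reduction on Days 1-3 | Interaction significant | Group effect significant |
|---|---|---|
| 0.5 SD | 0.047-0.054 | 0.33-0.50 |
| 0.8 SD | 0.047-0.052 | 0.69-0.88 |
| 1.0 SD | 0.051-0.053 | 0.86-0.97 |
| 1.5 SD | 0.048-0.052 | at least 0.995 |

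**Growing benefit, for contrast.** Take differences of 0, 0.5 and 1.0 SD on Days 1, 2 and 3. Then δ̄ = 0.5, Σ(δj − δ̄)² = 0.25 + 0 + 0.25 = 0.5, and λ = 7.5 × 0.5 / (1 − ρ) = 3.75 / (1 − ρ).

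| ρ | λ | Interaction significant | Group effect significant |
|---|---|---|---|
| 0.4 | 6.25 | 0.58 | 0.50 |
| 0.6 | 9.375 | 0.77 | 0.41 |
| 0.8 | 18.75 | 0.97 | 0.33 |

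Here the interaction test does better. The two tests answer different questions, and H1 as worded asks the one that the article does not name.

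**The case against.** The strongest reply is that the interaction is named only as the gate for post-hoc tests. A repeated-measures ANCOVA produces a group effect as a matter of course, and with two groups that effect needs no post-hoc test. Group descriptives are also planned, with CIs where appropriate. This stands in part. A reader might infer that a steady benefit would be reported as no effect, or that daily differences would never be shown. The document does not say so: what is conditional is post-hoc testing, not description. But unadjusted descriptives are not the adjusted difference with its interval, and the written criterion still does not use the effect that H1 describes.

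A reader might also call the interpreting sentence false. It is not; only its converse fails.

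A growing effect is plausible with six encounters over the first days, and the interaction would serve it well. Nor does the article fix the order of the Day 1 score and the first encounter. If that score came before any effect, the interaction would carry relevant information. Both points stand. They show that the interaction is worth reporting, not that it can stand in for H1, which covers all three days.

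The simulated power for the group effect rests on assumed correlations and ignores allocation by two-week blocks, so it may be optimistic. The zero interaction under an equal benefit depends on neither.

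Finally, a full analysis plan or the registry entry may say more. The point, however, is not missing detail: the article states a rule, and that rule does not match its hypothesis. The allowance for alternative methods is tied to model assumptions, not to which effect addresses H1.

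**Conclusion.** The point holds as a mismatch between H1 and the criterion written for it. Under a benefit equal on Days 1-3, the gate opens in about 5% of trials at any effect size. That result is exact and needs only the equal-benefit pattern and a level of 0.05. The gain from using the group effect is less certain: a 0.8 SD reduction would be detected in 0.69-0.88 of trials under the assumptions listed, and those figures are illustrative.

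It is tempting to treat this as a fault in the trial's main patient result. The article does not support that. H1 is one of six hypotheses under the secondary objective, the primary objective is acceptability and feasibility, and efficacy is explicitly not to be settled here. The consequence is a possibly misleading signal for the design of the larger trial, not a wrong confirmatory conclusion. The correction is worth making because a study that looks for trends is better served by estimates and intervals than by comparisons released only after a significant test.

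**What to change.** In Statistical methods, replace the two sentences on post-hoc tests and the meaning of the interaction with text to this effect:

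1. The H1 estimate is the group difference in Delirium Index averaged over Days 1-3, adjusted for ICDSC at onset, from the planned mixed model, with its 95% CI.
2. The adjusted group difference on each of Days 1, 2 and 3 is reported with its 95% CI whatever the interaction shows.
3. The group-by-time interaction is reported as a secondary description of the time course. Its absence is not read as absence of a group difference.

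It would also help to state whether the Day 1 Delirium Index is taken before or after the first encounter, because that decides how the interaction can be read.

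Cost: a few sentences of analysis text. The data, model and sample size stay the same.
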